## Abstract

**Background:**

Maintaining a sufficiently high systolic blood pressure is essential for free flap perfusion after microsurgical breast reconstruction. Yet, many women undergoing these procedures have low postoperative systolic blood pressure. Intravenous volume administration or vasopressors may be needed to maintain systolic blood pressure above a predefined threshold. However, excessive volume administration may lead to volume overload and flap stasis, and the postoperative use of vasopressors may be limited depending on institutional standards. Additional nonpharmacological measures to raise blood pressure might be beneficial. Evidence suggests that the Red Bull energy drink could raise blood pressure. It has been shown to increase systolic and diastolic blood pressure in healthy volunteers and athletes.

**Objective:**

The primary objective of this study is to determine the difference in systolic blood pressure between an intervention group receiving Red Bull and a control group receiving still water after microsurgical breast reconstruction. Secondary objectives include postoperative heart rate, 24-hour fluid balance, pain level, or necessity for revision surgery due to flap complications.

**Methods:**

The Red Bull study is a prospective, multicenter randomized controlled trial comparing the effect of postoperative ingestion of Red Bull energy drink against still water in female patients undergoing unilateral microsurgical breast reconstruction. A total of 250 mL of Red Bull (intervention group) or 250 mL of still water (control group) will be administered to the study participants 2 hours postoperatively as well as for breakfast and lunch on postoperative day 1, amounting to a total volume of 750 mL per 24 hours. Female patients between 18 and 70 years of age undergoing unilateral microsurgical breast reconstruction will be included. Exclusion criteria are a history of arterial hypertension, cardiac rhythm disorder, diabetes mellitus, gastric or duodenal ulcer, thyroid disease, and current use of antihypertensive or antiarrhythmic drugs or thyroid hormones, as well as intolerance to Red Bull.

**Results:**

Recruitment for the study started in June 2020 and was completed in December 2022. There is evidence that the Red Bull energy drink increases blood pressure in healthy volunteers and athletes. We hypothesize that postoperative ingestion of Red Bull will increase systolic blood pressure in women after microsurgical breast reconstruction. Red Bull could hence be used as a nonpharmacological adjunct to vasopressors or volume administration in women with hypotensive blood pressure after microsurgical breast reconstruction.

**Conclusions:**

This paper describes the Red Bull study trial protocol and analysis plan. The information will increase the transparency of the data analysis for the Red Bull study.

**Trial Registration:**

ClinicalTrials.gov NCT04397419; https://clinicaltrials.gov/ct2/show/NCT04397419

**International Registered Report Identifier (IRRID):**

DERR1-10.2196/38487

## Introduction

### Overview

Maintaining a sufficiently high systolic blood pressure is vital for free flap perfusion after microsurgical breast reconstruction. However, many women undergoing microsurgical breast reconstruction have low systolic blood pressure postoperatively. Often, intravenous volume administration or vasopressors are needed to maintain systolic blood pressure above 100 mm Hg. Yet, intravenous volume administration may lead to volume overload and flap stasis, and the use of vasopressors in the postoperative setting may be limited depending on institutional policies. Additional nonpharmacological measures to guarantee adequate postoperative perfusion pressure would be beneficial.

### Clinical Evidence for Red Bull Energy Drink

Red Bull energy drink has shown varying effects on the hemodynamic profile and pain perception in clinical studies performed on healthy participants and athletes [1-3]. A randomized crossover study showed a negative hemodynamic profile in response to Red Bull [2]. Participants who ingested 355 mL of Red Bull showed increased systolic and diastolic blood pressure, increased heart rate, and cardiac output without significantly reduced endothelial function compared with a control group who received 355 mL of tap water. This was reproduced in another randomized crossover study that further explored the combined effect of Red Bull and mental stress on cardiovascular parameters [1]. The combination of Red Bull and mental stress leads to an additional increase in systolic and diastolic blood pressure and heart rate, suggesting a cumulative effect.

Energy drinks have shown varying effects on endothelial function [4,5]. In a case report, a reduced reactive hyperemia index was observed after ingestion of Monster energy drink, suggesting worsened endothelial function [4]. In contrast, Red Bull improved endothelial function in a prospective study involving 6 volunteers [5]. Ingestion of 250 mL of Red Bull significantly increased endothelial function as measured by the reactive hyperemia index. In the same study, coffee containing comparable amounts of caffeine did not affect endothelial function. These results suggest that ingredients other than caffeine account for the vasodilatory effect.

Considering the mild diuretic effect of caffeine, Red Bull energy drink may increase urine formation rate and decrease urine specific gravity. Although urinary output increased with caffeine and Red Bull energy drink in 1 study [6], this trend could not be observed elsewhere [7].

Red Bull energy drink may furthermore increase pain tolerance [7]. Levels of pain after a cold pressor test were measured in participants before and after consumption of 250 mL of Red Bull. All participants reported a decreased perception of pain directly following Red Bull consumption.

### Interventional Product

Red Bull energy drink was first introduced in Austria in 1987 and launched in Switzerland in 1994. It is among the most popular energy drinks with over 6 billion cans being sold annually worldwide [8]. A can of 250 mL Red Bull energy drink contains 80 mg caffeine, 1 g taurine, 240 mg glucuronolactone, 27 g carbohydrates as well as water, sodium citrate, vitamins (B3, B5, B6, and B12), flavoring, and coloring agents [9]. This corresponds to total calorie content of 194 kJ (46 kcal) per 100 mL [8].

Despite anecdotal reports that linked Red Bull consumption with ventricular tachycardia and symptoms of cardiovascular disease, limited daily consumption of 500 mL of Red Bull appears safe [7,9]. When investigated in clinical studies no deleterious effects of Red Bull energy drink on cardiovascular function have been found [10]. Any adverse effects after excessive consumption are most likely due to the accumulation of caffeine, which is known to cause nervousness, anxiety, tremor, insomnia, tachycardia, arrhythmia, and nausea with ingestion exceeding 200 mg/day [11,12]. The amounts of taurine contained in Red Bull are far below the threshold to cause adverse effects [11].

Caffeine is an adenosine receptor antagonist with stimulating properties on the central nervous system It is known to increase blood pressure and peripheral vascular resistance through sympathetic stimulation [13]. Taurine is a sulfur-containing amino acid that constitutes the most abundant intracellular amino acid in humans [14]. Taurine seems to modulate skeletal muscle contractile function and possesses antiarrhythmic, inotropic, and chronotropic properties [15]. Glucuronolactone occurs naturally in small amounts within the body. Little data exists on its function in humans [9]. The amount of sugar provided in a can of 250 mL Red Bull energy drink is 27 g, which corresponds to 6.5 teaspoons of sugar [9]. Consuming moderately concentrated carbohydrate solutions (5%-8%) has been shown to promote prolonged exercise performance without causing adverse effects [15].

### Dose Rationale

The authors selected a daily administration of 250-500 mL of Red Bull in the study. Most investigators studied the effect of Red Bull after ingestion of 250, 355, or 500 mL. When ingested in standard amounts, Red Bull energy drink is a safe beverage without notable side effects [7,9].

### Risks

Daily oral administration of 500 mL of Red Bull has proven safe, and any side effects after consumption exceeding 500 mL daily have been linked to caffeine [9]. These include nervousness, anxiety, tremor, insomnia, tachycardia, arrhythmia, and nausea. To minimize adverse events, participants with allergies or intolerance to any component of Red Bull will be excluded from the study.

### Study Aim

The authors prospectively study the effect of postoperative ingestion of Red Bull energy drink on perfusion-related variables and patient recovery after microsurgical breast reconstruction. To our knowledge, there are no competing trials.

### Objectives

This study aims to assess perfusion-related variables, postoperative levels of pain, type of postoperative complications, operative reexploration rate due to complications, and total duration of hospital stay in patients undergoing autologous microsurgical breast reconstruction with postoperative ingestion of Red Bull Energy drink.

#### Primary Objective

The primary objective is to assess the difference in systolic blood pressure (mm Hg) between the intervention group and the control group at 15, 30, 45, 60, 75, 90, 105, and 120 minutes after each of 3 Red Bull (intervention group) or water (control group) applications.

#### Secondary Objective

The secondary objective is to document and assess the following variables in the intervention group and the control group:

Diastolic and mean arterial blood pressure (mm Hg) at 15, 30, 45, 60, 75, 90, 105, and 120 minutes after each of 3 Red Bull (intervention group) or water (control group) applications.Postoperative heart rate (1/min) at 15, 30, 45, 60, 75, 90, 105, and 120 minutes after each of 3 Red Bull (intervention group) or water (control group) applications.Postoperative urinary output (mL) during the first postoperative 24 hours.Intraoperative and postoperative fluid administration (mL) until 24 hours after surgery.Intraoperative and postoperative administration of vasoactive drugs (mg) until 24 hours after surgery.Postoperative pain (numeric rating scale [NRS]) during the first postoperative 24 hours.Postoperative administration of opioid analgesics (analgesic in mg).Postoperative administration of nonopioid analgesics (analgesic in mg).Postoperative administration of benzodiazepines (mg).Rate of operative reexplorations during the first hospitalization (%).Flap loss (%).Duration of hospital stay (number of nights spent at hospital).Wound healing 4 weeks after surgery (photo documentation).

#### Safety Objective

Notable adverse events of Red Bull energy drink in this population are as follows: nervousness, nausea, anxiety, tremor, insomnia, arrhythmia, need for revision surgery, and flap loss.

### Inclusion and Exclusion Criteria

Textbox 1 shows the inclusion and exclusion criteria.

As a standard of care, all patients are asked to perform a check-up by their general practitioner (GP) within 2-4 weeks before the microsurgical procedure. Their GP fills in a standardized form provided by the Institute of Anesthesiology, from which all inclusion and exclusion criteria can be drawn. Additionally, the GP performs an electrocardiogram and a blood test (complete blood count, electrolytes, creatinine, and international normalized ratio or Quick) for the patient and sends the result to the institute of anesthesiology at the respective clinic.

Inclusion and exclusion criteria.
**Inclusion criteria**
Female patients between 18 and 70 years of age.Ability to give written informed consent before participation in the study.Ability to comply with the requirements and restrictions listed in the consent form.
**Exclusion criteria**
History of arterial hypertension.History of cardiac rhythm disorder.History of diabetes mellitus.History of gastric or duodenal ulcer.History of hyperthyroidism or hypothyroidism.Current use of antihypertensive drugs, antiarrhythmic drugs, and thyroid hormones.Allergy or intolerance to the component of Red Bull energy drink.Not fulfilling inclusion criteria.

### Randomization and Blinding

Randomization is undertaken with equal allocation to each study group (Red Bull:still water=1:1) using a computed code. Blinding or masking is not feasible.

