### Sample Size

The following assumptions estimated from literature and clinical experience:

Mean systolic blood pressure (mm Hg): We assume the same SDs (ie, 15) for both groups and the correlation coefficient among repeated measures to be 0.7. If we assume no differences in time in the control group (mean 115 mm Hg) and assume the difference between the intervention group and the control group to be about 10 mm Hg, the required sample size would be 27 per group.Heart rate (1/min): We assume the same SDs (10) for both groups and the correlation among repeated measures to be 0.7. If we assume no differences in time in the control group (mean 80/min) and assume the difference between the intervention group and the control group to be 5/min, the required sample size would be 46 per group.Vasoactive drug Ephedrine (mg): We assume the mean drug dose in the control group to be 63 and the mean drug dose in the intervention group to be 48. Assuming equal SDs (ie, 25) we get 45 per group.

The predefined parameters include a significance level (α level) of .05 and power (1-β) of 0.8.

We calculated the patients needed to be included using the application STATA (version 15.1; StataCorp, 2017; Stata Statistical Software: Release 15) and G*Power (version 3.1.9.4—a program written by Franz Faul, Universität Kiel). Considering the different calculations and accounting for potential missing data or dropouts, 50 patients per group will be included, leading to a total of 100 patients.

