### Statistical Methods

We are planning to measure mean systolic blood pressure at 8 time points. For this, the right statistical model is a mixed ANOVA where the group is an independent (unpaired) factor, and the time is a dependent (paired) factor. The comparison of drug intake between the Red Bull group and the control group will be performed by student *t* test for independent data (assuming data will follow a normal distribution). In case data will not follow a normal distribution, an alternative nonparametric test will be used (Mann-Whitney *U* test).

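### Two clinics, but no centre term in the stated systolic pressure and drug-intake comparisons: a modest, avoidable loss of precision

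*Protocol article*

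**What the plan says.** All references are to the Protocol article. Study Population and Intervention place the trial at two clinics in Zurich. Randomization and Blinding describes the allocation in one sentence: "Randomization is undertaken with equal allocation to each study group (Red Bull:still water=1:1) using a computed code".

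Statistical Methods names the pressure model and its factors: a "mixed ANOVA where the group is an independent (unpaired) factor, and the time is a dependent (paired) factor". For drug dose it states: "The comparison of drug intake between the Red Bull group and the control group will be performed by student *t* test for independent data". A Mann-Whitney U test is the fallback if the data are not normal. Analysis Plan ties the analysis to these methods. Centre is in neither comparison.

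Three other places bear on the point. The Overview of the Introduction remarks that "the use of vasopressors in the postoperative setting may be limited depending on institutional policies". Intervention reports that perioperative procedures are standardised across the two clinics. Discussion dates database lock and data extraction to February 2023.

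**The concern.** Centre is a design feature of a two-site trial and a natural candidate prognostic factor. Staff and case mix can differ between clinics, and with them blood pressure and ephedrine dose. Systolic pressure is the primary outcome, and ephedrine dose is one of the three quantities on which the trial is sized.

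If the clinics differ and the model ignores it, two things follow. The between-clinic variance is counted as residual error, which widens the confidence interval for the treatment difference. In addition, if one arm happens to hold more women from one clinic, part of the clinic difference appears in the treatment estimate and nothing in the analysis removes it. What is at stake is power and the width of the interval, not validity.

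**Working it through.** **Inputs from Sample Size and Statistical Methods.** "The predefined parameters include a significance level (α level) of .05 and power (1-β) of 0.8"; sidedness is not given, so I take it as two-sided. Systolic pressure: "We assume the same SDs (ie, 15) for both groups and the correlation coefficient among repeated measures to be 0.7"; "difference between the intervention group and the control group to be about 10 mm Hg, the required sample size would be 27 per group"; 8 time points. Ephedrine: means of 63 and 48 mg (difference 15), SD 25, 45 per group. Planned size: 50 per group.

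**Inputs assumed.** The documents give neither a centre difference nor the split of women by clinic. I use centre differences of 0.2, 0.5 and 1.0 of the stated SD, with a 50:50 split and, as a check, 80:20.

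**Step 1: reproduce the plan's own figures.** For the between-group effect over m = 8 measures with correlation 0.7, the effective SD is 15 × √[(1 + 7 × 0.7)/8] = 15 × √0.7375 = 12.88 mm Hg. A difference of 10 mm Hg then needs 27 per group (normal approximation) or 28 (t), against 27 stated. Ephedrine needs 44 (normal) or 45 (t), against 45 stated. Both reproduce. Power at 50 per group is 97.0% for pressure and 84.4% for ephedrine.

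**Step 2: cost of leaving centre out if the stated SDs are within-centre.** The unadjusted variance is SD² + p(1 − p)Δ², where Δ is the centre difference and p the share of women at one clinic. With p = 0.5 the added term is Δ²/4. For example, pressure with Δ = 7.5 gives 165.9 + 14.1 = 180.0, SD 13.42. Ephedrine with Δ = 12.5 gives 625 + 39.1 = 664.1, SD 25.77. Noncentral-t power at 50 per group is:

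| Outcome | Centre difference | Power, no centre term | Power, centre term | Loss (points) |
|---|---|---|---|---|
| Pressure | 3 mm Hg (0.2 SD) | 96.8% | 97.0% | 0.2 |
| Pressure | 7.5 mm Hg (0.5 SD) | 95.8% | 97.0% | 1.2 |
| Pressure | 15 mm Hg (1 SD) | 91.3% | 97.0% | 5.7 |
| Ephedrine | 5 mg (0.2 SD) | 84.0% | 84.4% | 0.4 |
| Ephedrine | 12.5 mg (0.5 SD) | 82.2% | 84.4% | 2.2 |
| Ephedrine | 25 mg (1 SD) | 75.7% | 84.4% | 8.7 |

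The centre-term column ignores the one lost degree of freedom and any imbalance. With an 80:20 split the unadjusted figures are 96.9, 96.3 and 93.6% (pressure) and 84.2, 83.0 and 78.8% (ephedrine).

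**Step 3: if the stated SDs are already total SDs.** The unadjusted power stays as planned, at 97.0% and 84.4%. A centre term then gives a gain instead of preventing a loss. With a 50:50 split and the three centre differences, power becomes 97.2, 98.0 and 99.7% (pressure) and 84.7, 86.6 and 92.9% (ephedrine).

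**Step 4: chance imbalance under unstratified allocation.** The SD of the difference in clinic share between arms is √(2 × 0.25/50) = 0.10. The resulting SD of the treatment difference is 0.10 × Δ: 0.3, 0.75 and 1.5 mm Hg, and 0.5, 1.25 and 2.5 mg. These compare with planned differences of 10 mm Hg and 15 mg.

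**Step 5: simulation.** I used 10,000 runs per scenario with unstratified 1:1 allocation and centre differences of 0.5 and 1 SD. Type I error without a centre term was 4.6 to 4.8%. Simulated power without and with the term was 95.8 and 96.9% (pressure, 0.5 SD), 91.1 and 96.6% (pressure, 1 SD), 81.6 and 83.7% (ephedrine, 0.5 SD), and 75.4 and 83.7% (ephedrine, 1 SD). This agrees with Step 2 to within about a point.

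**The case against.** The strongest case against the point is that nothing in the documents says these two clinics differ. The remark on institutional policy is hedged background on why a non-drug measure might help. A reader might infer from it that vasopressor use differs between the trial's own centres, but it does not say so. The only statement about these clinics, in Intervention, points the other way. Surgeon is not shown to follow centre either, since the surgeons appear to be accredited at both. All of this stands, and it is why the size above is a range resting on assumed differences.

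A reader might also infer that allocation was not stratified. The article does not support that. A computed 1:1 code excludes neither blocks nor separate lists per clinic, and a condensed article may leave this to the full protocol. Recruitment has also ended, so nothing could be changed. If lists were kept per clinic, the chance-imbalance part largely falls away and the residual-variance part remains.

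A third objection is that covariates may be set out in a document not shown. Other Measures of Minimizing Bias does promise to bring caffeine intake and postoperative vasopressors into the analysis, so Statistical Methods is not a complete list. This stands only in part. Statistical Methods positively names the model and its factors, and Analysis Plan binds the analysis to them. The promised additions do not name centre, and vasopressor use after randomisation cannot stand in for a baseline factor.

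Finally, adding a covariate to an open-label trial after data extraction is a late change. That is fair, and it governs how the fix must be reported.

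**Conclusion.** The point holds as a minor one. The stated pressure and drug-intake comparisons omit centre in a two-centre trial, so any centre difference would stay in the error term and chance imbalance would go uncorrected. If the stated SDs are within-centre and the split is 50:50, the cost is about 1 power point for pressure and 2 for ephedrine at a centre difference of 0.5 SD, and about 6 and 9 points at 1 SD. Ephedrine falls below the planned 80% only in the 1 SD case, and pressure stays above 90% throughout. If the stated SDs are total SDs, planned power is intact and the centre term is a gain forgone.

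The omission should not be read as bias or as a threat to the 5% level. Chance imbalance is ordinary sampling error that the unadjusted standard error already reflects, and the simulation shows no inflation.

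**What to change.** Add centre as a fixed between-subject factor to the systolic pressure model. Compare ephedrine dose by a linear model on group and centre. If the nonparametric route is taken, use a van Elteren test stratified by centre in place of the Mann-Whitney U test.

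Because the database is already locked, date the change, declare it as made after lock, and report the stated unadjusted results alongside the adjusted ones.

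The cost is one degree of freedom and a late change to the analysis. No further patients or visits are needed. The article does not list centre among the recorded variables, so this assumes that each woman's clinic can be identified from the trial records.

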### Other Measures of Minimizing Bias

We will measure the systolic and diastolic blood pressure using ambulatory 24-hour blood pressure monitors (Tonoport VI, Anandic Medical Systems AG) to ensure comparable measurements (same side of arm and same cuff) and reduce intermeasurer variability. All patients will remain in bed during the first 12 hours postoperatively and will have a urinary catheter during this period. This further reduces changes in blood pressure not related to the study intervention. Additionally, all patients entering hospital preoperatively will have fasted for 6 hours (solids) and 2 hours (liquids). Also, oral fluid and food intake during the first 24 hours after a microsurgical procedure is typically low among all patients to ensure that patients could be taken back to theater in a timely manner should flap complications occur. The preoperative regular consumption of caffeinated products and the consumption of additional caffeinated products during the hospital stay will be recorded and incorporated in the final analysis. If a patient requires additional vasopressors postoperatively, this will be documented and incorporated in the final analysis.

